### Sample size

In the power calculation, we used the unpaired *t* test to detect a difference in the primary outcome (MISS-21) between the two groups. The RICS score, as the secondary outcome measure, was not used in the power calculation.

We incorporated the standard deviation in a nurse practitioner group in a trial using MISS-21 measurement [21]. There is, to date, no student data on MISS-21, and nurse practitioners are therefore chosen as the most likely comparator group. The medical student participants, in their first clinical year, are more likely still to be using a â€˜script-based’ clinical consultation style with less variability and are not considered comparable to experienced doctors. With 33 participants per group, there is 80% power of detecting a difference of at least 0.32 points in the MISS-21 at 5% significance level, assuming the standard deviation in the control group is 0.46 [21]. Cohen’s *d* = 0.69 indicates that a difference of 0.32 points has a moderate to large effect size in the primary outcome.

### Randomization

Assignment of interventions will be by block randomization, according to a list of computer-generated random numbers.

### Allocation concealment and blinding

Allocation numbers are kept in sealed containers. Tutor and patient assessors will be blinded to group membership. Emergency unblinding will be considered only on student participants’ request and approval. For example, a student may experience significant distress and request tutor counselling or debriefing after receiving written feedback.

Tutor assessors, patient assessors and data analysts are blinded to group assignment of participants. Because of the nature of the feedback, student participants will not be blinded to the group membership.

### Implementation

An investigator (ML) generates the allocation sequence using computer-generated numbers and conceals the random sequence in sealed opaque envelopes. Another investigator (NR), not directly involved in the assessment of students, draws the envelopes and assigns participants to their study groups.

Student participants are required to complete a common assessment battery at the time of enrolment: demography, baseline RICS and MISS-21 after their first consultation. At the end of baseline assessment, student participants are randomly allocated to the RICS group (control) or combining RICS and MISS-21 (intervention).

Students in the intervention group will be able to obtain MISS-21 patient satisfaction feedback no later than one week prior to the final consultation session near the end of the semester. They are requested to complete a reflection exercise using the Pendleton model [15]. Students in the control group will be able to obtain patient feedback using the MISS-21 within one month following their final consultation session (after the intervention period). Hence, the control group will still have an opportunity for self-reflection and benefit from patient feedback to improve their consultation skills.

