**Methods:**

The Patient Teaching Associate (PTA) Feedback Study is a single site randomized controlled, double-blinded trial with two parallel groups.

An after-hours general practitioner clinic in Victoria, Australia, is adapted as a teaching clinic during the day. Medical students from two universities in their first clinical year participate in six simulated clinical consultations with ambulatory patient volunteers living with chronic illness. Eligible students will be randomized in equal proportions to receive patient satisfaction score feedback with the usual multisource feedback and the usual multisource feedback alone as control. Block randomization will be performed. We will assess patient satisfaction and consultation performance outcomes at baseline and after one semester and will compare any change in mean scores at the last session from that at baseline. We will model data using regression analysis to determine any differences between intervention and control groups. Full ethical approval has been obtained for the study. This trial will comply with CONSORT guidelines and we will disseminate data at conferences and in peer-reviewed journals.

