## Methods/design

### Study design

The Patient Teaching Associate (PTA) Feedback Study is designed as a randomized, controlled, assessor- and patient-blinded, single-centre exploratory trial with two parallel groups after six student consultation sessions (Figure 1). The CONSORT statement has been used as the framework for the methodology of this study.

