### Interventions

Eligible students will be randomized in equal proportions to receive either patient satisfaction score feedback with usual verbal multisource feedback or usual verbal multisource feedback alone, as control.

Students in both the intervention and control group receive oral feedback from the tutor, PTA and peers immediately following each patient consultation. Both intervention and control groups receive immediate oral feedback according to the Rating Instrument of Clinical Consulting Skills (RICS) framework [13].

The educational intervention is written feedback using the 21-item Medical Interview Satisfaction Scale (MISS-21) in addition to the usual oral feedback [14]. The MISS-21 is a widely available 21-item validated visit-based questionnaire for measuring patient satisfaction in the primary care context. The MISS-21 questionnaire can be found in appendix 1 of the article by Meakin *et al.*
[14]. Students in the intervention group will receive their intervention pack no later than one week prior to the last consultation during one semester (generally six consultations in total). The intervention pack includes patient feedback questionnaires for all previous student-led consultations as well as written instructions about self-reflection on the feedback received based on the Pendleton feedback framework [15].

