### Primary outcome measure

The primary outcome measure is patient satisfaction immediately after the student consultation episodes, rated using the MISS-21 [14]. The consultation satisfaction questionnaire has been used to rate general practitioners and nurse practitioners. It is chosen because of its ease of administration, as it is visit-based and free from cost- or facility-based questions, has reported validity and reliability, and is a commonly used feedback tool in the consultation based clinical setting [16–18]. An independent researcher interviews each PTA after each consultation to obtain the scores.

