### Data management and statistical methods

All data will be entered electronically. The dataset will be recorded in a spreadsheet maintained on a secured University server. All forms related to the study will be kept in locked cabinets. Access to the study forms and electronic data will be restricted. All reports will be prepared such that no individual participant can be identified.

All data will be analyzed using SPSS (IBM Corp. Armonk, NY, USA.) and Stata (StataCorp LP, College Station TX, USA). We will compare student characteristics between the two groups using a chi-squared test for categorical variables and a *t* test for continuous variables. We will model data using regression analysis to assess any change in mean score on the MISS-21 and RICS patient-centeredness subscale (dependent variables) at the first and last tutorial session for both groups and to determine whether any differences exist between intervention and control groups (independent variables), taking the following covariates into account: age, sex, education in years, postgraduate status and international student status. They may enter the regression model only if the covariates are imbalanced between the two groups after randomization due to chance.

Additional subgroup analyses will be performed for the following variables: undergraduate versus postgraduate study, work experience, local versus international students status and language spoken at home.

There will be no control group for patient assessors. We will use linear mixed effects regression to account for random effects of variability in student grouping and variability in patient characteristics.

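### MISS-21 is scored after every consultation, but the stated analysis uses only the first and last sessions, so scores taken before the feedback pack is released are left unused and precision is lost

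*Protocol article*

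**What the plan says.** - **Baseline and allocation** (Implementation). The enrolment battery consists of "demography, baseline RICS and MISS-21 after their first consultation". Allocation follows directly: "At the end of baseline assessment, student participants are randomly allocated to the RICS group (control) or combining RICS and MISS-21 (intervention".
- **Delivery** (Interventions). Both arms receive the same oral feedback. The arms differ by the written pack: "Students in the intervention group will receive their intervention pack no later than one week prior to the last consultation during one semester", with six consultations being usual. On its content: "The intervention pack includes patient feedback questionnaires for all previous student-led consultations". Implementation also places delivery near the end of the semester.
- **Collection** (Primary outcome measure). "An independent researcher interviews each PTA after each consultation to obtain the scores".
- **Number of sessions** (Study design). The comparison is of "two parallel groups after six student consultation sessions".
- **Analysis**. The Abstract's Methods state that the investigators "will compare any change in mean scores at the last session from that at baseline". Data management and statistical methods describes a regression of change in mean MISS-21 and RICS patient-centredness scores "at the first and last tutorial session for both groups". It adds a linear mixed model with random effects for student grouping and patient characteristics, and names no term for the intermediate sessions.

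**The concern.** Because the pack contains the questionnaires from all preceding student-led consultations and comes near the end of the semester, the sessions between the first and the last appear to take place before anything differs between the arms. Scores from those sessions are then pre-intervention measurements that the trial already pays to collect. The stated analysis instead relies on one score, from the student's first consultation, to represent where the student started.

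A single score is a weaker predictor of the final score than the mean of several. At stake is precision in a trial of 33 per arm whose planned power is just at 80%. A linked point is the timing of allocation. The intermediate scores are secure baseline values only if students do not know their arm when the scores are taken and if no pack can be released before them. The article fixes neither.

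**Working it through.** **Inputs from the Protocol article (Sample size).** 33 students per arm, difference 0.32, SD 0.46, 5% level, unpaired t test. Sidedness is not stated; two-sided is used here, because a one-sided test would need only 26 per arm.

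**Assumed inputs.** The article gives no between-session correlation. I take a common correlation r between any two sessions, at 0.2, 0.3 and 0.5. The number of scored pre-pack sessions per student, m, is not stated either. The most it can be with six sessions is five: the baseline plus sessions 2 to 5.

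**Step 1: the plan's own figure.** The normal approximation gives 33 per arm, with power 80.7%. The noncentral t distribution with 64 df gives 79.5%. The stated figure reproduces. It uses no baseline information, so it does not depend on what follows.

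**Step 2: variance after adjustment.** The squared correlation between the mean of m equally correlated scores and a further score is

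R² = m r² / (1 + (m − 1) r).

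The residual variance of the last score is 0.46² × (1 − R²).

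- r = 0.2: m = 1, R² = 0.040; m = 2, 0.08/1.2 = 0.067; m = 5, 0.20/1.8 = 0.111.
- r = 0.3: m = 1, 0.090; m = 2, 0.18/1.3 = 0.138; m = 5, 0.45/2.2 = 0.205.
- r = 0.5: m = 1, 0.250; m = 2, 0.50/1.5 = 0.333; m = 5, 1.25/3 = 0.417.

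**Step 3: reduction in residual variance relative to one baseline score**, 1 − (1 − R²_m)/(1 − r²).

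| r | m = 2 | m = 5 |
|---|---|---|
| 0.2 | 1 − 0.933/0.960 = 3% | 1 − 0.889/0.960 = 7% |
| 0.3 | 1 − 0.862/0.910 = 5% | 1 − 0.795/0.910 = 13% |
| 0.5 | 1 − 0.667/0.750 = 11% | 1 − 0.583/0.750 = 22% |

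**Step 4: power for 0.32 points**, noncentral t, 33 per arm, 63 df (one covariate), SD = 0.46 × √(1 − R²).

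| r | m = 1 | m = 2 | m = 5 |
|---|---|---|---|
| 0.2 | 81.1% | 82.1% | 83.9% |
| 0.3 | 83.1% | 85.0% | 87.7% |
| 0.5 | 89.5% | 92.6% | 95.4% |

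**Step 5: if change is analysed as a plain difference.** The article does not say whether the first score is subtracted or entered as a covariate. Subtracting it gives variance 0.46² × 2(1 − r), with power 59.5%, 65.3% and 79.5% at r = 0.2, 0.3 and 0.5. Subtracting the mean of five scores gives a factor of 1 + (1 + 4r)/5 − 2r = 1.2(1 − r), which is 40% lower at any r. The tables above use the more favourable comparator, adjustment for the first score.

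**The case against.** **The analysis is valid as it stands.** Randomizing after a baseline assessment is ordinary practice, and the sample size is met without any of this gain. That is correct: the point concerns efficiency only.

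**A fuller plan may use the intermediate scores.** The article plans a mixed model and hypothesizes about satisfaction over time, and an unseen analysis plan could add the middle sessions. That is possible. But the article does name its two analysed time points, and the mixed model is described for grouping and patients, not for sessions. Nor are the scores discarded altogether, since they make up the pack.

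**Five scores is the best case.** Students attend in groups of three and the pack covers student-led consultations. If the three take turns, six sessions give about 6/3 = 2 led consultations each, perhaps only one of them before the pack, and then there is no gain. This stands, and is why the smaller cases are shown.

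**Equal correlation is a simplification.** Students are learning and patients vary, so the true gain may differ. This also stands.

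Three stronger readings are tempting:

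- *Allocation comes about five sessions too early.* With six sessions, at most four (2 to 5) lie between allocation and the pack. The pack has a latest date but no earliest one.
- *Students know their arm for most of the semester.* Allocation concealment and blinding says that students are not blinded because of the nature of the feedback, which fits learning the arm when the pack arrives. When they are told is not stated.
- *Early allocation costs drop-outs.* The article gives no loss figure and expects very high retention, so no size can be put on this.

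**Conclusion.** The point holds as a loss of precision. Scores from up to four intermediate sessions, collected anyway and apparently before the pack, play no part in the stated analysis. The estimate is not biased by this and the stated sample size is not wrong.

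The gain available runs from nothing (one pre-pack score per student) through 1 to 3 power points (two scores) to about 3 to 6 points (five scores) for r between 0.2 and 0.5. It rests on three things that the article does not give: the between-session correlation, the number of scored sessions per student, and delivery of the pack after the intermediate sessions. The last is implied by the pack's content and the late delivery date, but is not fixed. The change is worth making because it is nearly free and the planned power has no margin.

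**What to change.** 1. Make the primary between-group analysis the last-session MISS-21 score, adjusted for the mean of all of the student's MISS-21 scores obtained before pack release. Treat RICS in the same way where intermediate scores exist. State how many scored sessions per student are expected.
2. Keep the first-to-last comparison for the within-group aim of improvement from baseline, which a pre-pack mean would not serve.
3. Draw the envelopes only when packs are prepared, or at least disclose allocation to students only then. State that no pack is released until the next-to-last session has been held. The scores in the covariate are then true baseline values.
4. If the timing of allocation cannot move, fit a repeated-measures mixed model to all sessions, with the group effect estimated at the last one.

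Cost: a changed date for drawing or disclosing allocation, one added sentence on release, and revised analysis wording. No extra data, visits or participants are needed. The small downside is less time to make up the packs between allocation and release.

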### Adherence

We will recruit third-year medical students in their first clinical year to participate in the trial. This group of students is highly motivated in learning from real patient volunteers. A very high rate of retention and adherence in participation is expected.

Email adherence reminders will be sent after the participants have obtained written feedback of patient satisfaction. This reminder will emphasize the importance of following study guidelines to read the written feedback and the importance of contacting the coordinator if experiencing problems related to the study intervention. Debriefing and referral for counselling will be available to any student upon request.

### Data management and statistical methods

All data will be entered electronically. The dataset will be recorded in a spreadsheet maintained on a secured University server. All forms related to the study will be kept in locked cabinets. Access to the study forms and electronic data will be restricted. All reports will be prepared such that no individual participant can be identified.

All data will be analyzed using SPSS (IBM Corp. Armonk, NY, USA.) and Stata (StataCorp LP, College Station TX, USA). We will compare student characteristics between the two groups using a chi-squared test for categorical variables and a *t* test for continuous variables. We will model data using regression analysis to assess any change in mean score on the MISS-21 and RICS patient-centeredness subscale (dependent variables) at the first and last tutorial session for both groups and to determine whether any differences exist between intervention and control groups (independent variables), taking the following covariates into account: age, sex, education in years, postgraduate status and international student status. They may enter the regression model only if the covariates are imbalanced between the two groups after randomization due to chance.

Additional subgroup analyses will be performed for the following variables: undergraduate versus postgraduate study, work experience, local versus international students status and language spoken at home.

There will be no control group for patient assessors. We will use linear mixed effects regression to account for random effects of variability in student grouping and variability in patient characteristics.

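### The between-group analysis is described as a comparison of change in MISS-21 with no baseline covariate, but the 80% power is for a single score; the two agree only if baseline and final scores correlate at about 0.5 or more

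*Protocol article*

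**What the plan says.** **Analysis.** The abstract says the trial "will compare any change in mean scores at the last session from that at baseline". Under Data management and statistical methods the article says "We will model data using regression analysis to assess any change in mean score on the MISS-21 and RICS patient-centeredness subscale (dependent variables"). The scores in question are those from each arm's opening and closing sessions, and the article goes on to ask whether the groups differ. The covariates named there are age, sex, years of education, postgraduate status and international status. They are admitted only if chance leaves them imbalanced. Baseline MISS-21 is not on the list. The same section plans a linear mixed model with random effects for student grouping and patient characteristics.

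**Sample size.** The Sample size section says "we used the unpaired *t* test to detect a difference in the primary outcome (MISS-21) between the two groups", and concludes that "there is 80% power of detecting a difference of at least 0.32 points in the MISS-21 at 5% significance level". The SD behind this figure is 0.46, assigned to the control arm and borrowed from nurse practitioners in a cited trial. No SD of a change and no baseline-to-final correlation appears.

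**Timing.** The Implementation section has MISS-21 measured after the first consultation and randomization after that, so every randomized student should have a baseline score.

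**The concern.** A difference between two noisy scores carries the noise of both. If first and last scores are only weakly related, subtracting the baseline adds variance instead of removing it, and the comparison is less precise than one that ignores the baseline altogether. The power calculation contains no term for this: it uses one SD, on a scale completed per visit, in a two-sample t test.

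A weak correlation is possible here. Each MISS-21 score is one patient's rating of one consultation, and the first and last of about six consultations lie a semester apart. If r is low, the primary comparison of a 66-student trial with no allowance for dropout would have clearly less than the stated power. A chance difference between arms at baseline would also pass into the change score through regression to the mean, although this averages out over randomizations.

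**Working it through.** **Inputs from the Sample size section:** 33 per arm, difference 0.32, SD 0.46, 5% level. The test is taken as two-sided; the article does not say, but the two-sided version reproduces its figure and the one-sided version does not (87.5% power at 33 per arm).

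**Assumptions:** 0.46 is the SD of a single score; SDs are equal at first and last session; r is unknown, so a range is shown.

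**1. Reproduce the stated figure.** Standardized difference = 0.32 / 0.46 = 0.696. Standard error = 0.46 × √(2/33) = 0.113. Non-centrality = 0.32 / 0.113 = 2.83. Power is 79.5% by the noncentral t distribution (64 df) and 80.7% by the normal approximation, and the normal formula gives 33 per arm. The stated 80% is correct for a comparison of single scores.

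**2. Change score.** SD = 0.46 × √(2(1 − r)). For example, at r = 0.3: 0.46 × √1.4 = 0.544; standard error 0.544 × √(2/33) = 0.134; non-centrality 0.32 / 0.134 = 2.39; power 65%. A two-time-point model with an unconstrained group-by-time contrast has the same variance.

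**3. Last-session score adjusted for baseline.** SD = 0.46 × √(1 − r²), 63 df. At r = 0.3: 0.46 × √0.91 = 0.439; power 83%. This leaves out the small further cost of estimating the baseline slope.

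| r | SD of change | Power, change | Difference detectable at 80%, change | Power, baseline-adjusted final |
|---|---|---|---|---|
| 0 | 0.651 | 50% | 0.46 | 79.5% |
| 0.2 | 0.582 | 60% | 0.41 | 81% |
| 0.3 | 0.544 | 65% | 0.38 | 83% |
| 0.4 | 0.504 | 72% | 0.35 | 86% |
| 0.5 | 0.460 | 79.5% | 0.32 | 89% |
| 0.6 | 0.411 | 87.5% | 0.29 | about 93.5% |
| 0.7 | 0.356 | 95% | 0.25 | 97% |

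**4. Break-even.** The change comparison reaches 80% at r = 0.49 (normal) or 0.51 (noncentral t). Below that, the number per arm needed for 80% (normal formula) is 65 at r = 0, 52 at 0.2, 46 at 0.3 and 39 at 0.4.

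**5. Change against adjusted final score.** The variance ratio is 2(1 − r) / (1 − r²) = 2 / (1 + r): 2.0 at r = 0, 1.33 at r = 0.5, 1.18 at r = 0.7. It is never below 1, so the preference for adjustment does not depend on the value of r. Only the size of the gain does.

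**The case against.** **Baseline adjustment is not ruled out.** This stands. No sentence forbids it; its absence is read from the covariate list. The wording also fits a model of both time points, and one that constrains the arms to a common baseline mean would be about as efficient as adjustment. But nothing in the article specifies that constraint, and random effects for student group and patient do not supply it.

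**The change wording serves a second purpose.** This also stands in part. Objectives and hypothesis includes a separate hypothesis of improvement over time, and the Discussion separates within-group improvement from the comparison of arms. Any fix must leave that analysis in place. The abstract nevertheless describes the comparison itself as one of change.

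**r may exceed 0.5.** It may, and the change comparison then meets or exceeds 80%: 87.5% at r = 0.6 and 95% at 0.7. A reader might infer that the trial is underpowered; with r undocumented, the article does not support that.

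**0.46 might not be a single-visit SD.** The source is not at hand. A single score is the natural reading of a visit-based scale, an unpaired t test and an SD assigned to the control group, but the article does not say so outright.

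**The change comparison is valid.** Correct. Under randomization it is unbiased with the nominal type I error, and the article calls the trial exploratory. A reader might also infer that a change outcome leaves the planned patient random effect with no single patient to attach to; in a two-time-point model each session's record has its own patient, so that does not follow.

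**Conclusion.** The point holds as a mismatch between the power statement and the described analysis, and as an avoidable loss of precision. As described, the between-group comparison has the stated 80% power only if r is about 0.5 or more; it is 50% to 72% for r from 0 to 0.4, and above 80% for r of 0.6 or 0.7. Adjusting the last-session score for baseline gives about 79.5% or more at every r from 0 upward.

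This rests on 0.46 being a single-score SD, on equal SDs at both sessions, and on reading the covariate list as complete. It does not show that the stated power will be missed, that the estimate is biased or that the test is invalid. Clustering of students in threes and dropout are separate matters and are not in these figures.

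**What to change.** For the primary between-group comparison, make the last-session MISS-21 score the dependent variable, with arm and baseline MISS-21 as fixed terms that are always in the model and do not depend on observed imbalance, inside the planned mixed model. An equivalent choice is a two-time-point mixed model with a common baseline mean for the two arms. Treat the RICS outcome the same way, with its own baseline.

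State in the Sample size section that the 80% refers to a comparison of last-session scores. With respect to baseline correlation that figure is then approximately a floor; it does not cover clustering or dropout.

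Keep the analysis of change from first to last session as a separate analysis for the over-time hypothesis.

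The cost is wording and one degree of freedom. Baseline scores are already planned for every student before randomization, so no new data are needed.

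### Five covariates may enter the regression only if they look imbalanced between arms, so adjustment follows chance rather than prognostic value and precision is forgone

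*Protocol article*

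**What the plan says.** All of the relevant text is in the Protocol article.

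- **Model.** Data management and statistical methods: "We will model data using regression analysis to assess any change in mean score on the MISS-21 and RICS patient-centeredness subscale" between the first and last session, with group as the explanatory variable, "taking the following covariates into account: age, sex, education in years, postgraduate status and international student status".
- **Entry rule.** The next sentence restricts those five covariates: "They may enter the regression model only if the covariates are imbalanced between the two groups after randomization due to chance".
- **Baseline comparison.** The same paragraph says "We will compare student characteristics between the two groups using a chi-squared test for categorical variables", with a t test for continuous ones. It does not say that these tests operate the entry rule, and it gives no threshold for imbalance.
- **Allocation.** Randomization: "Assignment of interventions will be by block randomization, according to a list of computer-generated random numbers". No stratification factor is named.
- **Baseline outcome.** Implementation: students complete "baseline RICS and MISS-21 after their first consultation", and are allocated after that. The baseline score is used through the change from first to last session. It is not on the covariate list.

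The later sentence on linear mixed effects regression deals with student grouping and patient variability. It neither fixes the covariate set nor overrides the entry rule.

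**The concern.** Randomization guarantees that differences in baseline characteristics between arms are chance, as the rule itself acknowledges. Observed imbalance therefore tells the analyst nothing about whether a covariate predicts MISS-21 change. A covariate gains precision by explaining outcome variance, and that gain is available when it is balanced too. Under the rule, a strongly prognostic covariate that happens to be balanced is kept out, and an uninformative one that happens to be imbalanced may come in.

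The fitted model also depends on the data. Five candidates allow 2^5 = 32 covariate sets, and which one applies is known only after the arms have been compared. The rule covers both the primary outcome and the RICS patient-centeredness analysis. The trial is sized at about 80% power with no stated dropout allowance, so cheap precision is worth having.

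**Working it through.** **Inputs from the Sample size section:** 33 per group, difference Δ = 0.32, SD σ = 0.46, 5% significance (two-sided assumed), unpaired t test. **Inputs assumed because the article gives none:** the trigger for imbalance, and the share R² of outcome variance that a covariate explains.

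**1. The article's own figure.** d = 0.32/0.46 = 0.696. Normal approximation: 0.696 × √(33/2) = 2.826; Φ(2.826 − 1.960) = 80.7%, and the required n is 33 per group. The noncentral t gives 79.5%. The stated 80% is reproduced. It rests on no covariate adjustment.

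**2. How often the rule would add a covariate.** If the trigger is a baseline test at level a and the five covariates are independent, P(at least one enters) = 1 − (1 − a)^5:

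- a = 0.05: 1 − 0.95^5 = 22.6%
- a = 0.10: 1 − 0.90^5 = 41.0%
- a = 0.20: 1 − 0.80^5 = 67.2%

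At a = 0.05 the model stays unadjusted about 77% of the time, however prognostic the covariates are. Independence is generous: if age, education in years and postgraduate status correlate at an assumed 0.8, the 22.6% falls to about 18%.

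**3. Power with one covariate always included, against the rule.** Adjustment reduces the residual SD to σ√(1 − R²), so approximate power is Φ(2.826/√(1 − R²) − 1.960). This ignores the lost degree of freedom and chance imbalance and so runs about one point high. The last two columns are simulated with 33 per arm and an assumed p<0.05 trigger.

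| Assumed R² | 2.826/√(1 − R²) | Approximate power | Always adjusted | Imbalance rule |
|---|---|---|---|---|
| 0 | 2.826 | 80.7% | about 80% | about 80% |
| 0.10 | 2.979 | 84.6% | about 83% | about 79% |
| 0.15 | 3.065 | 86.5% | about 86% | about 81% |
| 0.30 | 3.377 | 92.2% | about 91% | about 80% |

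Under the rule, power stays where the unadjusted test puts it.

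**4. All five covariates forced in.** Simulated power, fixed five-covariate model against the rule: R² = 0, 77.0% v 79.4%; R² = 0.10, 80.4% v 78.6%; R² = 0.30, 89.5% v 80.5%. A long set costs power when it is uninformative, so the fixed set should be short.

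**5. Type I error under the rule.** With one covariate, about 4.7 to 5.0%. With five covariates, 4.9% at R² = 0, 4.7% at 0.10, 4.4% at 0.30 and 3.4% at 0.50. Error is nominal or below it.

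**The case against.** The strongest reply is that nothing planned is lost. The sample size rests on an unadjusted t test, and power under the rule remains about 80%. The gain depends on an R² that the article does not give, and nothing shows that these student characteristics explain much of the change in MISS-21. The Study design section calls the trial exploratory, and data analysts are blinded to assignment, which limits any steering of the model towards one arm. A condensed article may also leave the threshold to a fuller document. All of this stands, and it limits the size of the point. It does not defend the rule: selecting on imbalance is stated affirmatively, and a fuller document could cure it only by reversing it.

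Four stronger readings are tempting but unsupported:

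- *The baseline tests at 5% decide which covariates enter.* The article never links the tests to the rule and states no threshold, so the percentages above are conditional on an assumed trigger.
- *The rule inflates false positives.* The simulated error rate is at or below 5%.
- *The trial is underpowered because of the rule.* The planned power is still met; what is lost is a possible gain.
- *Prognostic adjustment is thrown away altogether.* The baseline score is used in part through the change score, and the listed covariates can still enter when imbalanced.

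**Conclusion.** The point holds as a matter of method and efficiency. The entry rule chooses adjustment on chance imbalance and leaves the model open until the arms have been compared. It does not threaten the trial's validity, its error rate or its sample size.

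For one always-included covariate, the forgone power is nil at R² = 0, about 4 to 5 points at R² = 0.10 to 0.15 and about 11 points at R² = 0.30. These figures assume a p<0.05 trigger, a two-sided 5% test, independent students and ordinary regression. They do not model the groups of three or the planned mixed model, so they indicate scale rather than exact operating characteristics. The objection to selecting on imbalance does not depend on the trigger or on R²; only the size of the loss does.

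**What to change.** Delete the sentence that makes entry conditional on imbalance. In its place, prespecify a short adjustment set that is always included:

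- the baseline score of the outcome being analysed, which is already collected before allocation; and
- at most one or two of the five listed covariates, named in advance because the investigators expect them to predict the outcome. The article does not say which these are, so the choice is theirs to make and record.

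Fit this set within the planned mixed effects model, and report baseline characteristics by arm descriptively, without significance tests.

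No new data are needed and the sample size stays at 66. The cost is one to three degrees of freedom and, if a chosen covariate turns out not to be prognostic, about one point of power or less for each.
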